#### Control group

The control group will receive usual care which consists of any activities undertaken by the participants that are recommended or administered by their treating team. In addition, control participants will receive a general information booklet on falls prevention (developed by Peninsula Health Falls Prevention Service, Victoria, Australia).

#### Outcomes

The primary outcome for this study will be the incidence of falls in the 12 month period post-discharge. Based on the definition by Lamb et al [47] a fall is defined as a sudden, unexpected event in which an individual comes to rest on the ground, the floor, or other surface. A lay perspective of this definition will be provided to participants to assist with ascertainment of falls [47]. Falls will be monitored prospectively using a falls calendar supplied to participants. Participants will complete a tear-off calendar page each month marking any falls that have occurred. In addition, information about each fall will be collected such as location, activity prior to fall, injuries sustained, and medical treatment required. The calendar page will be returned to study personnel using pre-paid envelopes after the end of each month. Follow-up calls to those who do not return calendar pages within 2 weeks of the end of the month will be undertaken to ensure complete data. The researcher collating information about falls and undertaking the follow-up phone calls will be blind to group allocation.

Secondary outcomes will include the following:

(i) functional lower limb muscle strength (5-STS) [32],

(ii) gait and balance measures (5mwt-comf, 5mwt-fast [33], ST [29], TUG-single [34], TUG-dual [35])

(iii) activity level (HAP-AAS) [36],

(iv) participation (LHS) [38],

(v) function (FIM^®^) [37],

(vi) fear of falling (FES-S) [39,40],

(vii) falls risk (FROP-Com) [31].

In addition, time taken to first fall, and fall injury severity will be evaluated.

The research physiotherapist conducting the 12 month follow-up assessment will be blind to group allocation and participants will be specifically instructed not to reveal their group allocation to the researcher.

#### Sample Size

It is estimated that in the usual care group, 75% of participants will experience a fall in the 12 month follow up period (given their increased risk of falling as outlined in the project inclusion criteria [9]), and that the intervention would reduce this incidence by one third to 50%. Based on 90% power to detect a significant difference (p = 0.05, two-sided), 85 participants are required for each arm of the study. Allowing for a 25% dropout rate, we plan to enrol 107 participants in each group giving a total sample of 214.

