#### Sample size

It is estimated that approximately half of the overall sample will be included in this sub-study, giving a sample size of 80. The sample will include participants from the control and intervention arms of the main study.

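### The 25% dropout allowance multiplies 85 by 1.25 instead of dividing by 0.75, so 107 per arm leaves about 80 completers and about 88% power on the plan's own sizing basis (minor)

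*Protocol article*

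**What the plan says.** The calculation is in the protocol article under Randomised controlled trial, Sample Size. It rests on the proportion of participants who fall at least once:

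- Control arm: "It is estimated that in the usual care group, 75% of participants will experience a fall in the 12 month follow up period".
- Intervention arm: a relative reduction of one third, to 50%.
- Operating characteristics: "Based on 90% power to detect a significant difference" ("p = 0.05, two-sided").
- Requirement: "85 participants are required for each arm of the study".
- Enrolment: "Allowing for a 25% dropout rate, we plan to enrol 107 participants in each group giving a total sample of 214".

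The section names no test or formula and does not define the dropout rate in any special way. The Statistical methods section that follows plans an intention-to-treat comparison of falls by negative binomial regression. It gives unequal follow-up time as one reason for that choice.

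**The concern.** The section gives a requirement (85 per arm), a loss rate (25%) and an enrolment target (107 per arm). With a dropout rate read in the usual way, as a share of those enrolled, the three do not fit together. If the requirement and the loss rate stand, the target is too low. If the target and the loss rate stand, the number completing falls below the requirement, and the 90% power claim no longer follows. At stake is the accuracy of a headline design statement that readers will use to judge how much loss the trial can absorb.

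**Working it through.** **Inputs**, all from the Sample Size section: p1 = 0.75, p2 = 0.50, two-sided alpha = 0.05 (z = 1.960), power = 0.90 (z = 1.282), dropout = 0.25, enrolled = 107 per arm.

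**Step 1. Reproduce the 85.** The mean proportion is 0.625 and the difference is 0.25.

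- Uncorrected: n = [1.960 x sqrt(2 x 0.625 x 0.375) + 1.282 x sqrt(0.75 x 0.25 + 0.50 x 0.50)]^2 / 0.25^2 = 76.7, so 77 per arm.
- With the Fleiss continuity correction: n' = (n/4) x [1 + sqrt(1 + 4/(n x 0.25))]^2 = (76.7/4) x [1 + sqrt(1 + 4/(76.7 x 0.25))]^2 = 84.5, so 85 per arm.

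The stated 85 is reproduced by the continuity-corrected formula. The other variants tried do not give it: 74 with unpooled variance, 77 with arcsine, and 63 or 71 one-sided.

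**Step 2. Reproduce the 107.**

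- Multiplying: 85 x 1.25 = 106.25, rounded up to 107. This is the stated figure.
- Dividing by the retained fraction: 85 / 0.75 = 113.3, rounded up to 114 per arm, 228 in total. Check: 114 x 0.75 = 85.5.

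The gap of 7 per arm (14 in total) is too large to be rounding. Starting from the uncorrected 77 does not give 107 either: 77 / 0.75 = 102.7 (103) and 77 x 1.25 = 96.25 (97).

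**Step 3. What 107 delivers.**

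- Completers at 25% dropout: 107 x 0.75 = 80.25 per arm, about 5 below 85.
- Largest dropout that still leaves 85: 1 - 85/107 = 0.206, or about 20%. Check: 107 x 0.80 = 85.6.

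**Step 4. Power for 75% v 50%, completers only.**

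| Method | 80 per arm | 85 per arm |
|---|---|---|
| Continuity-corrected | 88.2% | 90.2% |
| Fisher's exact test | 88.3% | 90.1% |
| Uncorrected | 91.2% | 92.7% |

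For the first entry, the corrected difference is 0.25 - 1/80 = 0.2375, and power = Phi{[0.2375 - 1.960 x sqrt(0.46875/80)] / sqrt(0.4375/80)} = Phi(1.18) = 88.2%. Here 0.46875 = 2 x 0.625 x 0.375 and 0.4375 = 0.75 x 0.25 + 0.50 x 0.50.

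**The case against.** **The planned analysis does not discard dropouts.** This is the strongest counter-argument, and most of it stands. The primary comparison is negative binomial regression under intention to treat. The Outcomes section has falls recorded on monthly calendars, with calls to those who do not return a page. A participant who leaves midway still contributes the months observed. As an illustration, with timing assumed because the protocol gives none: if the 25% leave evenly over the year, 107 enrolled yield 80.25 + 26.75 x 0.5 = 93.6 person-years per arm, more than the 85 from 85 full-year completers. Break-even comes at (85 - 80.25)/26.75 = 0.178 of a year, about 2.1 months of average follow-up among dropouts. Person-years are only a rough guide to information in a negative binomial model, so this shows direction and not a power figure. It does not repair the sentence, because the trial was sized on the proportion falling over 12 months and the allowance was applied to that number.

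**Power stays above 90% without the continuity correction.** True, at 91.2%. The section names no formula, so the corrected basis is inferred from its reproducing 85. But on the uncorrected basis the requirement would have been 77, not 85. The point limits the consequence and leaves the inconsistency.

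**The 25% might mean 25% of the number required.** On that reading the multiplication would be right, but the loss among those enrolled would then be only about 20%. The text gives no such definition.

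**The sub-study size.** A reader might take the Fear of Falling Sub-Study, described as about half of the overall sample and "giving a sample size of 80", as confirmation, since half of 214 x 0.75 = 160.5 is about 80. That section does not mention dropout or retained numbers, and 80 is also not far from half of 170 (2 x 85). The match may be coincidence and carries no weight here.

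**Conclusion.** Wrong as written, minor in severity. The enrolment figure does not follow from the stated requirement and dropout rate: 107 was reached by multiplying, where division gives 114. At 25% dropout about 80 per arm complete, 5 short of 85. Power for the fallers comparison is then about 88% on the basis that reproduces 85, roughly 2 points under the stated 90%, and 91% uncorrected. These power figures assume that dropouts contribute nothing and that the comparison is a completers-only test of proportions.

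A reader might infer that the trial is underpowered for its primary analysis, or that it must recruit more. The documents support neither. The sample size was not derived for the negative binomial comparison, and that analysis can use partial follow-up, so the loss there is probably smaller than 2 points. No estimate or test in the plan is affected.

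**What to change.** Keep 214 enrolled and correct the last sentence of the Sample Size section in one of two ways:

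- Keep the 25% assumption and report what it implies: *with 25% dropout, about 80 participants per arm are expected to complete follow-up, giving about 88% power for the comparison of fallers (continuity-corrected)*.
- Report what the target can absorb: *107 participants per arm preserves 85 completers provided dropout does not exceed about 20%*. This should be worded as the limit of the design and not as a new forecast, because nothing in the article supports expecting 20% rather than 25%.

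Either version could add that dropouts' partial follow-up enters the negative binomial analysis. The cost is one sentence and a slightly less favourable statement of power or tolerable dropout. The figure of 114 per arm (228) is what 85 completers at 25% dropout would imply. Given the size of the effect, extra enrolment is not asked for.

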#### Statistical methods

Intention to treat analysis will be used. To compare falls in the intervention and control groups, negative binomial regression will be used. This model is appropriate as falls are recurrent events which are not normally distributed and follow up time is different for individuals [48]. Fall data will also be summarised as the fall rate per person year, time to first fall, as well as the number of falls, number of fallers, non-fallers and frequent fallers (two or more falls) [47]. Repeated measures analysis of variance will be used to determine differences in secondary outcomes between control and intervention groups from baseline to follow up, with a p-value set at < 0.05.

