### Randomised controlled trial

#### Participants

Stroke survivors aged forty-five years and over who have completed rehabilitation and have been discharged home will be eligible for the study if they have decreased balance or if they have fallen at any time during their hospital admission. Decreased balance is defined as a step test [29] worst leg score of less than 7 or a Berg Balance Scale [30] score of less than 49. These inclusion criteria were selected as it has been shown that decreased balance as defined above or a fall in hospital are predictors of multiple falls in the first 6 months after discharge from stroke rehabilitation [6]. Stroke sub-types will include infarct and haemorrhage (including sub-arachnoid haemorrhage) but will exclude sub-dural haemorrhage or infarct or haemorrhage due to malignancy. Those being discharged to residential care facilities and those being discharged more than one hundred kilometres from study sites will not be eligible.

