**Figure 1 F1:**
[figure not shown]
**Study design – randomised controlled trial**.

(i) falls risk, using the Falls Risk for Older People in the Community (FROP-Com) [31],

(ii) functional lower limb strength measured by the five chair sit-to-stand test (5-STS) [32],

(iii) gait and balance, measured by gait velocity over 5 metres at self-selected comfortable and fast pace (5mwt-comf, 5mwt-fast) [33], Step Test (ST) [29], and Timed Up and Go with and without a secondary cognitive task (TUG-single, TUG-dual) [34,35],

(iv) activity measured by the Human Activity Profile Adjusted Activity Score (HAP-AAS) [36], and

(v) function, as measured by FIM ^® ^[37].

In addition, the following stroke specific measures will be included at baseline:

(i) participation, measured by the London Handicap Scale (LHS) [38],

(ii) fear of falling, measured by the Falls Efficacy Scale (Swedish Modification (FES-S) [39,40],

(iii) inattention, assessed by the Baking Tray Task (BTT) [41] and the Star Cancellation Test (SCT) [42],

(iv) visual field, assessed by the Visual Field Confrontation Test (VFT) [43], and

(v) frontal function as measured by the Frontal Assessment Battery (FAB) [44].

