#### Randomisation

Participants will be assessed for eligibility, provided with information about the study, provide informed consent, be enrolled into the study and complete the baseline assessment prior to allocation into the control or intervention group. Participants will be assigned to the control or intervention arm of the study according to a computer generated random allocation sequence concealed from the researchers in opaque envelopes. Staff not involved in the study will undertake the sequence and concealment. The envelopes containing the allocation will be stored in one location and participants will be assigned in order of completed baseline assessment.

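### The primary negative binomial comparison names no baseline covariates; prespecifying a few would be a cheap, modest improvement

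*Protocol article*

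**What the plan says.** The primary endpoint is given under Outcomes: "The primary outcome for this study will be the incidence of falls in the 12 month period post-discharge". Under Statistical methods for the randomised trial the analysis is by intention to treat, and "To compare falls in the intervention and control groups, negative binomial regression will be used". The reasons given are that falls recur, are not normally distributed, and are observed over unequal follow-up. No covariate is listed. The model is not called unadjusted, and adjustment is not ruled out.

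Four other places bear on this:

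- **Participants** justifies the entry criteria on the ground that "decreased balance as defined above or a fall in hospital are predictors of multiple falls in the first 6 months" after discharge. Either feature is enough for entry.
- **Procedures** lists, among the baseline measures, "falls risk, using the Falls Risk for Older People in the Community (FROP-Com") and the Step Test. Under Randomisation, baseline assessment is completed before allocation.
- **Randomisation** describes a "computer generated random allocation sequence" held in opaque envelopes, with no stratification factor mentioned. Settings/locations gives nine health services in two cities.
- **Obstacle Crossing Sub-Study, Statistical Analysis** does state covariate adjustment, using covariates found to differ between the groups at that measurement session.

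**The concern.** Because either criterion admits a participant, the sample can mix people who fell in hospital but balance well, people with poor balance and no in-hospital fall, and people with both. Their fall rates may differ. If the model contains only arm, that variation goes into the dispersion parameter, which is a large part of the standard error of a negative binomial rate ratio. A chance imbalance in baseline risk between arms also stays in the point estimate. No stratification is described that would limit it.

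Two things are at stake: some precision, and how robust the result looks if baseline risk turns out uneven. There is also a prespecification point. The only adjustment rule in the article, in the obstacle-crossing sub-study, picks covariates by observed group differences. Naming the primary covariates beforehand keeps that practice out of the main comparison.

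**Working it through.** **Inputs from the protocol (Sample Size).** In usual care, "75% of participants will experience a fall in the 12 month follow up period"; "the intervention would reduce this incidence by one third to 50" per cent; "Based on 90% power to detect a significant difference (p = 0.05, two-sided), 85 participants are required for each arm of the study"; 25% dropout; 107 enrolled per arm.

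**Inputs not in the protocol, so assumed.** Dispersion k (1 to 3), mean fall rate (set to match 75% fallers), rate ratio, and the share R of between-person variation that the covariates explain (10%, 30%, 50%).

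**Step 1: reproduce the plan's figure.**
n = [1.960√(2×0.625×0.375) + 1.282√(0.75×0.25 + 0.50×0.50)]² / 0.25² = 76.7, so 77. With continuity correction, (n/4)[1 + √(1 + 4/(0.25n))]² = 84.5, so 85 per arm, which matches. After 25% dropout, 107 × 0.75 ≈ 80 complete per arm. Power for 75% v 50%, without continuity correction, is 92.7% at 85 and 91.2% at 80.

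**Step 2: convert the planned effect to rates.** Under a negative binomial model P(no fall) = (1 + kμ)^(−1/k).

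| k | control mean (75% fall) | intervention mean (50% fall) | rate ratio |
|---|---|---|---|
| 1 | 3.0 | 1.0 | 0.33 |
| 2 | 7.5 | 1.5 | 0.20 |
| 3 | 21 | 2.33 | 0.11 |

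Unadjusted Var(log RR) = (1/μ0 + 1/μ1 + 2k)/n. At k = 1, n = 80: (1/3 + 1 + 2)/80 = 0.0417, SE 0.204, z = 1.099/0.204 = 5.4. Power exceeds 99% for k = 1, 2 and 3.

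**Step 3: a smaller effect.** Read the one-third reduction as a rate ratio of 0.667 instead. At k = 1, (1/3 + 1/2 + 2)/80 = 0.0354, SE 0.188, z = 0.405/0.188 = 2.15, power 58%. At k = 2 and 3 it is 41% and 31%. This is not the planned effect: at k = 1 the intervention mean is 2, so 1 − 1/(1+2) = 67% fall, not 50%.

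**Step 4: gain from adjustment.** The simple formula replaces k by k(1 − R). At k = 1 and rate ratio 0.667, R = 30% cuts the variance by 0.6/2.833 = 21%. Over k = 1 to 3 and rate ratios 0.5 and 0.667, the cuts are 7–10%, 20–29% and 33–49% for R = 10%, 30% and 50%.

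Fitting both models to simulated data (80 per arm, 250 replicates, Monte Carlo error about 3 points on power) gives smaller cuts:

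| k | rate ratio | R | variance cut | power, unadjusted → adjusted |
|---|---|---|---|---|
| 1 | 0.667 | 10% | 2% | 55% → 57% |
| 1 | 0.667 | 30% | 10% | 60% → 62% |
| 1 | 0.667 | 50% | 21% | 60% → 74% |
| 2 | 0.667 | 10% | 2% | 46% → 45% |
| 2 | 0.667 | 30% | 12% | 52% → 54% |
| 2 | 0.667 | 50% | 22% | 55% → 65% |

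Each row has its own simulated data, so unadjusted power differs between rows. At rate ratio 0.5 unadjusted power is about 86–98% and adjustment changes it by between about 0 and +8 points.

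A second simulation (400 replicates, rate ratio 0.667, control mean 3) used a binary in-hospital fall with 40% prevalence plus the Step Test. At k = 1, with the two explaining 8%, 20% and 32% of the dispersion, the SE fell by 2%, 6–7% and about 10%. That is a variance cut of about 4%, 12–14% and 19%. With the same predictor effects at k = 2 the SE fell by 1%, 4% and 6%.

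**Step 5: chance imbalance.** Assume 30–50% of participants fell in hospital. With 107 per arm and no stratification, the SE of the difference in proportions is √(2×0.3×0.7/107) = 0.063 to √(2×0.5×0.5/107) = 0.068. A gap of 10 points or more has probability 11–14%. If prior fallers fall at 1.5 to 2 times the rate and the arms hold 45% and 35% of them, the rate ratio shifts by 1.225/1.175 = 1.04 to 1.45/1.35 = 1.07, that is 4–7%.

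**The case against.** The strongest reply is that this treats silence as a decision. The text is a journal article; a fuller protocol or analysis plan may list covariates and the offset, and leaving such detail to those documents is normal. That stands: the article does not commit to an unadjusted model, and nothing in it is stated wrongly. What remains is that the one description available names no covariate for the main comparison while naming adjustment for a sub-study, and that a better model can be specified largely from data already collected.

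Three further objections also stand.

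- A reader might infer that the predictors are strong. The article gives no strength, and they are the entry criteria, so everyone enrolled has at least one and selection may weaken them within the trial.
- A reader might infer that the trial needs this precision. On the protocol's own 75% v 50% it does not (Steps 1 and 2). The 58% power in Step 3 comes from an assumed smaller effect.
- In-hospital fall appears only as one of two routes to eligibility. It is not in the baseline list, and the article does not say it is recorded for people who qualify on balance.

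Finally, a randomised unadjusted comparison is unbiased, and its standard error already allows for chance imbalance. That is correct, so this is a question of efficiency and robustness, not validity.

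**Conclusion.** The point holds as a low-severity improvement. The primary comparison, as described, names no baseline covariates although the protocol itself identifies predictors of falls, measures balance and falls risk before allocation, and describes no stratification. Adjustment would cut the variance of the log rate ratio by roughly 2–4%, 10–12% or 20–22% when the covariates explain 10%, 30% or 50% of between-person variation (80 completers per arm, k = 1 or 2). The second simulation gives somewhat larger cuts at k = 1, and the simple formula larger still. The direction is consistent, but the size cannot be fixed from the document.

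The power gain matters only if the true effect is nearer a one-third cut in fall rate. Even then it runs from about nil to about 14 points, and the larger gains appear only when half the variation is explained. Protection against chance imbalance does not depend on the trial being short of power. The documents do not support a conclusion that the planned analysis is invalid, that it is definitely unadjusted, or that the trial is underpowered for its stated effect without adjustment.

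**What to change.** State the primary model in one sentence: negative binomial regression of the number of falls on arm, baseline Step Test worst-leg score (or FROP-Com), fall during the hospital admission (yes/no) and city (Melbourne or Adelaide), with log follow-up time as offset. Report the unadjusted rate ratio as a sensitivity result. With a log link and no interaction, both models target the same rate ratio, so the two can be read side by side. Fix the list before any outcome data are examined by arm, and do not choose covariates by observed group differences.

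The cost is three extra terms in a trial enrolling 214. The Step Test and FROP-Com are already collected and city is known. In-hospital fall needs a check that it is recorded at screening for everyone, including those who qualify on balance. If it is not, either record it for all or leave it out.

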#### Procedures

Figure 1 depicts the study design. Participants will be assessed at baseline (following recruitment) and after 12 months in the study. Baseline assessment will include the following general measures:

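### Secondary outcomes: with two assessments, the planned repeated-measures ANOVA is a valid change-score test, but adjusting the 12-month value for baseline is more precise and costs nothing

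*Protocol article*

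**What the plan says.** For the randomised trial, the Statistical methods section states: "Repeated measures analysis of variance will be used to determine differences in secondary outcomes between control and intervention groups from baseline to follow up". The significance level given there for these comparisons is 0.05, and no baseline covariate is named for them. The same section opens with "Intention to treat analysis will be used".

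The Procedures section fixes the schedule: "Participants will be assessed at baseline (following recruitment) and after 12 months in the study". Four-monthly visits appear only in the Fear of Falling Sub-Study. That covers the Melbourne participants, about half the sample, and only fear of falling, gait, balance and activity. For the trial comparison there are therefore two time points.

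The Outcomes section lists eleven scored secondary measures: 5-STS, two gait speeds, Step Test, two Timed Up and Go versions, HAP-AAS, LHS, FIM, FES-S and FROP-Com. All eleven are also in the baseline assessment. Time to first fall and injury severity are extra outcomes with no baseline value and are not part of this point.

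On numbers, the Sample Size section says: "Allowing for a 25% dropout rate, we plan to enrol 107 participants in each group giving a total sample of 214".

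**The concern.** Repeated-measures ANOVA on one baseline and one follow-up value compares the arms on mean change. Subtracting the whole baseline value gives it a weight of one, whatever its correlation with the 12-month value. When the correlation is below one, that over-corrects and adds noise. Regression on baseline estimates the weight from the data.

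What is at stake is the width of the confidence intervals, and so the power, for eleven measures of strength, gait, balance, activity, participation, function, fear of falling and falls risk. The article gives no power figure for any of them. A second, conditional matter is sensitivity to dropout: if those who stay differ in baseline between arms, a change score carries part of that imbalance into the treatment effect.

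**Working it through.** **Inputs.** From the article: two assessments; 107 enrolled per arm; 25% dropout; alpha 0.05 (taken as two-sided, as in Sample Size). Assumed: rho from 0.3 to 0.9, and equal SDs at baseline and 12 months unless stated.

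**The plan's own figure.** The article gives no precision or power figure for secondary outcomes. Its primary sample size reproduces. For 75% v 50%, two-sided 0.05 and 90% power, n = [1.960·√(2·0.625·0.375) + 1.282·√(0.1875 + 0.25)]² / 0.25² = 76.7, or 77 per arm; with continuity correction it is 85, as stated. Then 85 × 1.25 = 106.25, rounded up to 107. At 25% dropout, 107 × 0.75 = 80.25, so about 80 per arm have a 12-month value. That is the n used below.

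**Step 1: the planned test is a change-score test.** In a simulated data set with 80 per arm, the group-by-time F was 9.6153 and the squared t on change scores was 9.6153.

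**Step 2: variance.** Let s0 and s1 be the baseline and 12-month SDs.
- Change score: s0² + s1² − 2·rho·s0·s1.
- ANCOVA residual: s1²(1 − rho²).
- Difference: (s0 − rho·s1)², which is never negative.

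So, apart from one degree of freedom, the change score cannot be more precise. With s0 = s1 the two variances are 2(1 − rho) and 1 − rho² in units of s², and their ratio is (1 + rho)/2.

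| rho | Change variance | ANCOVA variance | Ratio | Reduction | Extra participants the change score needs |
|---|---|---|---|---|---|
| 0.3 | 1.40 | 0.91 | 0.65 | 35% | 54% |
| 0.5 | 1.00 | 0.75 | 0.75 | 25% | 33% |
| 0.7 | 0.60 | 0.51 | 0.85 | 15% | 18% |
| 0.9 | 0.20 | 0.19 | 0.95 | 5% | 5% |

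**Step 3: what this means with 80 per arm.** The detectable difference at 80% power, in SD units, is (1.960 + 0.842)·√(2·variance/80). For rho 0.3 this is 2.802·√(2·1.40/80) = 0.52 for change and 2.802·√(2·0.91/80) = 0.42 for ANCOVA.

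| rho | Detectable, change | Detectable, ANCOVA | Power at 0.4 SD, change | Power at 0.4 SD, ANCOVA |
|---|---|---|---|---|
| 0.3 | 0.52 | 0.42 | 57% | 76% |
| 0.5 | 0.44 | 0.38 | 72% | 83% |
| 0.7 | 0.34 | 0.32 | 90% | 94% |
| 0.9 | 0.20 | 0.19 | about 100% | about 100% |

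The 0.4 SD effect is illustrative.

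**Step 4: dropout.** Trials of 214 with a true effect of 0.40 SD were simulated, 4,000 runs per setting.
- *Random dropout, 25%.* Both methods averaged about 0.40 at rho 0.5, 0.7 and 0.9. The simulated standard errors at rho 0.5 were 0.160 (change) and 0.138 (ANCOVA); (0.138/0.160)² = 0.74, in line with Step 2.
- *Dropout depending on baseline, in opposite directions by arm* (log-odds −1.2 plus or minus the standardised baseline; about 27% missing). The change score averaged 0.63, 0.54 and 0.45 at rho 0.5, 0.7 and 0.9. ANCOVA stayed at 0.40.

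The change-score bias is (1 − rho) times the baseline gap between the arms' remaining participants: 0.229/0.5 and 0.137/0.3 both give a gap of about 0.46 SD.

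**The case against.** The strongest case against is that this is a preference about efficiency. In a randomised trial the between-arm comparison of change is a valid test, it concerns secondary outcomes only, and the gain depends on a correlation that the article does not report. At rho 0.9 the variance falls by only 5%, and the detectable difference moves from 0.20 to 0.19 SD. All of that stands. It limits the size of the point, but not its direction, because baseline adjustment is never worse beyond one degree of freedom.

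The bias result rests on an assumed dropout mechanism. The article gives a single overall 25% rate and does not suggest that loss will differ by arm. That also stands, so the advantage is conditional.

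A reader might infer three stronger things that the article does not support.
- *That intention to treat is claimed for a completer analysis, with about 54 of 214 (214 × 0.25 = 53.5) excluded, and that ANCOVA would repair this.* The article does not restrict the analysis to completers, and the handling of missing assessments may lie in a fuller document. Nor would ANCOVA repair it, since it uses the same participants with a 12-month value. A mixed model with a common baseline mean does not change this when only follow-up is missing. Its likelihood separates into a baseline part and a follow-up-given-baseline part, so the maximum-likelihood arm effect is the ANCOVA estimate. In one simulated trial of 214 with 55 missing, both gave 0.4364.
- *That the group main effect, diluted by the pre-randomisation value, would be reported as the treatment effect.* The wording describes differences between arms from baseline to follow-up, which points to the interaction.
- *That the planned analysis is wrong.* It is not; it is less efficient.

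**Conclusion.** The point holds as a free gain in precision for the eleven secondary measures. With equal variances, baseline adjustment lowers the variance of the treatment effect by 35% to 5% over rho 0.3 to 0.9. The gain is material at rho 0.5 or below (power for 0.4 SD rises from 72% to 83% at 0.5) and small near 0.9. Both rho and the equality of variances are assumptions; without equal variances the direction is unchanged, but the size becomes (s0 − rho·s1)².

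There is a further, conditional advantage if dropout depends on the measured baseline value and differs by arm. It assumes that the 12-month value is linear in baseline with a common slope, as in the simulation. The planned test is not invalid, the intention-to-treat statement is not contradicted, and the primary negative binomial comparison of falls is unaffected.

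**What to change.** Replace the repeated-measures sentence for the randomised trial with one stating that each of the eleven secondary measures will be analysed by ANCOVA: 12-month value as outcome, arm and that measure's own baseline value as covariates, with the adjusted 12-month mean difference and its 95% CI reported as the treatment effect. A mixed model for both assessments with a common baseline mean is an acceptable alternative and gives essentially the same arm effect.

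The cost is one sentence. No new data, visits or participants are needed. The change does not deal with missing 12-month values; how those are handled has to be specified separately.
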